## Results

Overview

The study was funded in 2024 and data collection began in July 2024. A total of 26 mothers in each group have participated. As of February 2025, the laboratory analysis is ongoing for the second step. We expect the results to be published at the end of 2025.

### Expected Outcomes

#### Reduction in Blood Heavy Metal Levels

The primary outcome of this study is the reduction in blood Pb/Cd/Hg level. The hypothesis is that supplementation with *M. oleifera* will result in a reduction in the blood levels of heavy metals in pregnant women compared to those in the control group. Hence, the expected results are as follows: (1) A measurable decrease in the blood Pb/Cd/Hg concentration will be observed in the group receiving *M. oleifera* supplementation for 2 months. (2) The intervention group is expected to show a greater reduction in blood heavy metal levels than the control group, based on pre- and post-test analyses.

Scientific implications expected are that the result would provide evidence that *M. oleifera* has the potential to detoxify, thereby demonstrating that it is a safe and effective approach to reducing heavy metal accumulation in expectant mothers, who are at a higher risk of exposure to environmental pollutants.

#### Reduction in 8-OHdG and MDA Concentrations

Hypothesis: *M. oleifera* will reduce 8-OHdG and MDA levels in pregnant women compared with the control group.

The expected results are as follows: (1) Significant reduction in 8-OHdG and MDA levels in the intervention group, indicating a protective effect against oxidative stress and DNA damage. (2) The intervention group will show lower levels of 8-OHdG and MDA after the intervention than the control group.

These findings will indicate that the antioxidant compounds of *M. oleifera* are effective in inhibiting DNA damage and protecting cells against oxidative stress. This is especially important for pregnant women to ensure fetal health and reduce complications.

#### Safety and Tolerability of *M. oleifera*

Hypothesis: *M. oleifera* supplementation will be safe for pregnant women, with no significant adverse effects reported during the intervention period. Hence, the expected results are as follows: (1) Minimal to no adverse effects in the group receiving *M. oleifera* supplementation. (2) This safety profile is consistent with previous studies indicating that 2000 mg/day is safe for pregnant women.

This will provide further evidence that *M. oleifera* is a safe supplement for pregnant women, supporting its use in future clinical applications and maternal health programs.

In the final analysis, changes in heavy metal levels (Pb, Cd, and Hg) will be reported individually, as well as in aggregate if appropriate. Similarly, biomarkers of oxidative stress (8-OHdG and MDA) will be analyzed and reported separately. While the study is not powered for definitive subgroup comparisons, exploratory reporting by relevant characteristics (eg, trimester, nutritional status, and baseline exposure level) will be presented to generate hypotheses for future studies.

## Discussion

### Principal Anticipated Findings

This study is expected to demonstrate that *M. oleifera* supplementation during pregnancy reduces blood levels of heavy metals and decreases oxidative stress biomarkers (8-OHdG and MDA). It also aims to confirm the safety and tolerability of moringa in pregnant women, laying the groundwork for its use as a low-cost, locally available intervention for mitigating environmental pollutant-related health risks.

Several animal studies have shown that moringa leaf extracts can significantly reduce heavy metal accumulation in vital organs and mitigate oxidative stress caused by Pb, Cd, and Hg exposure. These effects are attributed to its high content of flavonoids, phenolic acids, glucosinolates, and carotenoids, which act as free radical scavengers and binders of toxic metals.

While direct clinical evidence in pregnant women remains limited, moringa has been used traditionally in many parts of Indonesia and other countries as a nutritional supplement and natural remedy, including during pregnancy. Small-scale human studies in nonpregnant populations have reported improvements in antioxidant status and reductions in lipid peroxidation following moringa supplementation. This study assumes that the biological mechanisms observed in preclinical research—namely, antioxidant protection and chelation of toxic metals—will translate to similar detoxifying effects in pregnant women.

Importantly, while this study does not evaluate direct clinical outcomes (eg, birth weight, gestational age), the primary focus is on biomarker-based improvements, which are commonly used as surrogate indicators of fetal and maternal risk. The findings are expected to strengthen the biological plausibility for moringa as a preventive intervention in polluted environments and inform the design of future clinical outcome studies.

While the study aims to demonstrate reductions in blood heavy metals and oxidative stress biomarkers following *M. oleifera* supplementation, such findings—if observed—should be interpreted with caution. Positive outcomes would indicate that moringa is a promising candidate for reducing biochemical risk factors associated with environmental exposures in pregnancy. However, this study does not assess long-term or clinical outcomes (eg, fetal growth and birth weight) and therefore cannot confirm improvements in maternal or fetal health. Additionally, the study does not evaluate cost-effectiveness or scalability of implementation.

Conversely, if no significant effects are observed, several factors could explain this, including insufficient dosage, short intervention duration, limited sample size, or individual variability in absorption or baseline exposure. These considerations will guide future study design and refinement of the intervention strategy. Ultimately, findings from this study should be viewed as hypothesis-generating, laying the groundwork for larger, randomized trials with extended follow-up and clinical endpoints.

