**Conclusions:**

This study is expected to provide preliminary evidence on the potential effectiveness and safety of *M. oleifera* supplementation for reducing heavy metal toxicity and oxidative stress in pregnant women.

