### Intervention Group

In addition to receiving iron capsules, which are standard supplements provided by the health centers as part of the national prenatal care program, participants in the intervention group also received *M. oleifera* extract supplementation at a dose of 2000 mg/day, administered as 2 capsules taken twice daily (totaling 2000 mg/day) for a continuous period of 8 weeks. Supplementation began immediately upon enrollment, which occurred between gestational weeks 20 and 32. Therefore, the regimen lasted from the time of enrollment until 8 weeks later, typically ending between weeks 28 and 40 of gestation. For participants enrolled in the late third trimester who delivered before completing the full 8 weeks, they were instructed to continue consuming the remaining *M. oleifera* supplements until the full course was completed. This approach aimed to ensure consistency in the intervention dosage, regardless of the timing of delivery, and to maintain the study’s internal validity.

To support adherence, we collaborated with health cadres at each participating health center. The cadres will be responsible for supervising, reminding, and ensuring that the mothers consistently take the moringa capsules. A WhatsApp group was established specifically for the cadres to facilitate regular communication, provide reminders, and monitor the supervision process throughout the 8-week supplementation period. We have also added a simple adherence log that will be maintained by the cadres, documenting capsule intake daily based on direct questioning or observation. These dual approaches—cadre monitoring and pill counts—will allow us to triangulate adherence data and better distinguish true intervention effects from variability due to compliance.

Participants will be actively monitored for adverse events throughout the 8-week intervention period. At the follow-up visit, participants will be asked about any symptoms or side effects experienced, using a structured checklist and open-ended questions. Specific adverse events of interest include gastrointestinal discomfort (nausea, vomiting, and diarrhea), allergic reactions (skin rash and swelling), and general intolerance to the supplement.

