### Dissemination Plan

The findings of this study will be disseminated through peer-reviewed journal publications, conference presentations, and policy briefs to local and national health stakeholders. Collaboration with the Makassar City Health Office is planned to integrate results into maternal health programs. Community workshops will also be organized to share findings with participants and local health workers, promoting the evidence-based use of moringa.

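### The article says the study will confirm that moringa is safe in pregnancy, but with 26 to 59 treated women it can only describe tolerability

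*Protocol article*

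**What the plan says.** Three places state a safety conclusion.

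- **Expected Outcomes, Safety and Tolerability of *M. oleifera*.** The hypothesis is that the supplement will be safe for pregnant women. The expected result is "Minimal to no adverse effects in the group receiving" moringa. This is said to add to the evidence that it is a safe supplement, "supporting its use in future clinical applications and maternal health programs".
- **Discussion, Principal Anticipated Findings.** "It also aims to confirm the safety and tolerability of moringa in pregnant women". No evidential basis is named there.
- **Expected Outcomes, Reduction in Blood Heavy Metal Levels.** A fall in blood metals would show a detoxifying potential, "thereby demonstrating that it is a safe and effective approach to reducing heavy metal accumulation in expectant mothers".

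Other places are more cautious. The abstract's conclusion reads "This study is expected to provide preliminary evidence on the potential effectiveness and safety of" moringa. Later in the Discussion, "findings from this study should be viewed as hypothesis-generating". Strengths and Limitations and the Conclusion also call the findings preliminary.

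The safety methods stand under Intervention Group: "Participants will be actively monitored for adverse events throughout the 8-week intervention period". A structured checklist with open questions is used at the follow-up visit. Serious events and pregnancy complications are recorded and reviewed by the study physician. Safety data are to be summarized in the final report.

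The Dissemination Plan adds: "Collaboration with the Makassar City Health Office is planned to integrate results into maternal health programs".

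**The concern.** To confirm safety, a study must be able to rule out harm at a rate that would matter. The sample size calculation under Participant Recruitment is built on 8-OHdG alone. The safety hypothesis names no acceptable event rate, margin or comparison with controls. In a group this small, seeing few or no events is what one would often expect even if a harm of several percent existed.

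The inference from blood metals has a different fault. A lower metal level bears on efficacy and says nothing about harm, whatever the sample size.

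At stake is how the result is used. The safety text ties it to maternal health programs, and the Dissemination Plan provides a route to the city health office. If the wording is carried into the report, an event count from a few dozen women could be read as shown safety in pregnancy.

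**Working it through.** **The plan's own figure.** There is none for safety. The 37 per group in Participant Recruitment concerns 8-OHdG, and this point does not depend on it.

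**Inputs from the article.** Women per group: 26 have participated (Results, Overview); 44 after the dropout allowance and 59 to be included (both in Participant Recruitment). The study is described as ongoing, so all three are shown.

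**1. Upper limit on the true rate with zero events.** One-sided 95%: 1 − 0.05^(1/n). Two-sided exact 95%: 1 − 0.025^(1/n).

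| n treated | one-sided 95% | two-sided exact 95% |
|---|---|---|
| 26 | 1 − 0.05^(1/26) = 10.9% | 1 − 0.025^(1/26) = 13.2% |
| 44 | 6.6% | 8.0% |
| 59 | 5.0% | 6.1% |

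These limits need no assumed event rate. With one event in 26 the exact (Clopper-Pearson) limits are 17.0% and 19.6%.

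**2. Chance of seeing no case of a real harm**, (1 − p)^n. The rates p are illustrative and not in the article.

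- p = 2%: 0.98^26 = 59%; 0.98^59 = 30%.
- p = 5%: 0.95^26 = 26%; 0.95^59 = 4.8%.

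**3. Women needed, all without an event, to exclude a rate p** at one-sided 95%, ln 0.05 / ln(1 − p), rounded up.

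- p = 1%: 299.
- p = 2%: 149.
- p = 5%: 59.

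So the largest planned group, with no event at all, would just exclude 5%.

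**4. Would a comparison with controls rescue the claim?** Approximate 95% half-width of the risk difference at 26 v 26, with the same assumed risk p in both arms: 1.96 × √(2p(1 − p)/26).

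- p = 5%: 12 percentage points.
- p = 10%: 16 points.
- p = 20%: 22 points.

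Power to detect a doubling (two-sided 5% test) is 10% for 5% v 10% and 17% for 10% v 20% at 26 per group. At 59 per group it is 18% and 33%. These figures treat women as independent. The arms are also separated by health center, so a difference could reflect the center as well as the capsules.

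**5. Internal consistency.** An aim to confirm safety and an abstract that promises preliminary evidence on safety cannot both describe the same study. The arithmetic supports the abstract.

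**The case against.** The strongest reply is that the strong wording stands in sections on hoped-for results. The operative plan, under Intervention Group, is to record safety data and summarize them, which is already descriptive. Data Analysis describes no safety test or decision rule. The abstract limits the safety claim by name, the safety section itself speaks of further evidence, and Strengths and Limitations cites sample size. The adverse events of interest are mainly gastrointestinal and allergic, so this is largely a tolerability assessment. The Dissemination Plan speaks of results and does not mention safety, so misuse depends on the report ignoring its own caveats.

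Most of this stands and lowers the severity. It does not remove the defect: the caveats contradict the aim to confirm safety rather than qualify it, and the program-use inference is attached to the safety result itself.

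A reader might infer three stronger points that the document does not support.

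- *All three statements infer safety from a low event count.* Only the safety section does so. The metals section argues from blood levels, and the Discussion gives no basis.
- *Controls are not monitored for adverse events.* The recording is described under Intervention Group and not repeated under Control Group, but its text says participants, and controls have a 2-month visit. Control recording is unstated in a condensed article; it is not shown to be absent.
- *The prior safety evidence is overstated.* That depends on cited sources that are not at hand, so it is not claimed here.

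**Conclusion.** The concern holds as a mismatch between stated conclusions and what the design can show. Zero events would leave a true rate of up to 10.9% at 26 women, 6.6% at 44 and 5.0% at 59 (one-sided 95%), or 13.2%, 8.0% and 6.1% (two-sided exact). Calling moringa safe because blood metals fall is unsupported at any size.

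Severity is minor to moderate. The article already calls its findings preliminary, and its working plan for safety is a summary. It would be wrong to read this as a flawed safety analysis or as a study without caveats.

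The zero-event limits assume only that every treated woman is followed and events are fully recorded; losses would widen them. The 2% and 5% harm rates and the 5%, 10% and 20% arm risks are assumptions for scale, and the verdict does not rest on them.

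**What to change.** 1. **Expected Outcomes, Safety and Tolerability.** Replace the safety hypothesis with estimation of the proportion of women with each adverse event, with exact 95% limits. Delete the inference that the result supports use in clinical applications and maternal health programs.
2. **Discussion, Principal Anticipated Findings.** Replace the aim of confirming safety and tolerability with describing tolerability in the women treated.
3. **Expected Outcomes, Reduction in Blood Heavy Metal Levels.** Remove the word safe from the inference drawn from blood metals.
4. **Dissemination Plan.** Give any safety result passed to the health office with its upper limit.
5. **Controls.** If not already done, ask the same adverse event checklist at their existing 2-month visit. Preeclampsia, gestational diabetes and preterm labor also occur without moringa, so a count from one arm is hard to read. Where visits have passed without the checklist, say so. Treat any comparison between arms as descriptive, because the arms differ by center.

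The cost is a few wording changes, one table with limits and possibly a short checklist for controls. Dose, sample size and efficacy analysis are unchanged. The downside is a less favorable safety statement with wide limits.

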### Comparison to Prior Work

Previous studies have supported the antioxidant potential of *M. oleifera*, particularly its ability to reduce oxidative stress. For instance, in infertile women, moringa supplementation reduced oxidative stress markers and slightly increased antioxidant biomarkers, suggesting potential benefits for reproductive health [38]. Another study [39] demonstrated that supplementation with moringa leaf extract decreased levels of MDA in pregnant women, suggesting its role in reducing lipid peroxidation. This supports the hypothesis of the present study regarding moringa’s capacity to attenuate oxidative stress.

However, while there is growing interest in the detoxifying potential of moringa, evidence of its effect on heavy metal levels in humans remains limited. Currently, most studies demonstrating metal-chelating and detoxification effects of moringa have been conducted in animal models [40-46], showing efficacy in reducing Hg, Pb, and Cd accumulation. These include experimental studies in rodents that found significant reductions in blood and tissue metal concentrations after moringa supplementation.

This study extends this line of research by being one of the first protocol studies designed to evaluate whether these benefits translate into pregnant human populations exposed to environmental heavy metals. By integrating biomarker-based outcomes (heavy metals, 8-OHdG, and MDA), this study aims to address a critical evidence gap in prenatal environmental health interventions.

Thus, if our hypothesis is confirmed, it will add to a growing body of evidence supporting the nutritional role of antioxidant-rich plants in maternal health and offer novel evidence of moringa’s detoxifying role in reducing human heavy metal burden during pregnancy.

### Strengths and Limitations

This study has several limitations that should be acknowledged. First, the nonrandomized design introduces a risk of selection bias and limits internal validity. While the selection of different locations for the intervention and control groups was based on logistical and feasibility considerations, this may lead to differences in participant characteristics and environmental exposures. To mitigate this, statistical adjustments such as ANCOVA will be used, and effort has been made to select sites with comparable demographic profiles.

Second, blinding was not feasible in this trial—neither participants nor investigators are blinded to the intervention. This raises the potential for performance and detection bias, although this risk is minimized by the use of objective laboratory-based biomarkers assessed by independent laboratory technicians.

Third, the sample size may limit statistical power, particularly for detecting small effects or conducting subgroup analyses. As a result, findings from this study should be interpreted as preliminary and exploratory, forming a basis for future hypothesis-driven studies.

Fourth, the short duration of intervention (2 mo) and the use of biomarkers instead of clinical outcomes (such as birth weight or gestational age) limit the ability to draw conclusions about long-term maternal or fetal health impacts. While changes in oxidative stress and metal levels are valuable surrogate outcomes, future studies should evaluate direct clinical endpoints.

Finally, although both study groups were drawn from similar urban settings, environmental variability (eg, differences in pollution sources or background exposure levels) may confound the results. These residual environmental factors could influence outcomes independently of the intervention and are difficult to fully control.

Despite these limitations, the study addresses an important gap by testing a locally available, low-cost, and traditionally accepted intervention in a vulnerable population. Its findings will help guide the development of larger, more rigorous trials in the future.

### Conclusion

If our hypothesis is confirmed, moringa supplementation may offer a promising, locally available intervention for mitigating metal-induced oxidative stress during pregnancy. However, conclusions must remain preliminary until supported by completed trial data.

### Future Directions

Future studies should consider RCTs with larger sample sizes and multicenter recruitment to confirm causality. Investigating the dose-response relationship of moringa and including additional biomarkers (eg, GPx and catalase) would offer deeper insights into its antioxidant mechanisms. Longitudinal studies can assess whether reductions in oxidative stress lead to better birth and developmental outcomes. Future research should explore whether reductions in heavy metals and oxidative stress markers translate to improved birth outcomes, such as birth weight, gestational age, or neurodevelopmental status.

### Dissemination Plan

The findings of this study will be disseminated through peer-reviewed journal publications, conference presentations, and policy briefs to local and national health stakeholders. Collaboration with the Makassar City Health Office is planned to integrate results into maternal health programs. Community workshops will also be organized to share findings with participants and local health workers, promoting the evidence-based use of moringa.
